#### Sample size

In order to estimate the numbers of subjects and subject participation years required to obtain these numbers of births given that subjects are enrolled at pre-conception, we use a birth rate of 0.0957 births per subject-year, which is the rate observed to date in the ongoing study. Subject participation years are included in the fifth column of Table
8.

For the primary hypothesis, a total of about 16,531 subject-years are potentially required to provide the 1,582 births. Doubling the birth rate (0.19) would decrease the number of required subject years for all scenarios by half; about 8,266 total subject years will be needed to obtain 1,582 births. We believe the 0.0957 rate is conservative and underestimates the birth rate likely to be observed in this study due to the short period on which it is based and given that at least half of the subjects enrolled to date have expressed a desire to have (more) children. Any increase in the birth rate will result in a proportional decrease in the total required subject years.

Our estimate of the targeted sample size of subjects uses the estimate of 16,531 subject participation years as the lower bound for targeted subject years and takes into account the recruitment capacities of the participating sites. We will enroll about 21 subjects per week across the 4 sites using the clinic-based model (6 subjects in each of HRAC, Recife, and Salvador, and 3 in Porto Alegre) during the first four years, which are expected to provide about 12,035 subject-years, and will enroll about 1000 subjects by the end of the first year using the outreach model at the Bauru site, which are expected to provide about 4,250 subject years. Follow-up of subjects is scheduled to be completed about nine months after the end of recruitment. The 550 subjects currently participating in the study at Porto Alegre, Salvador, and Bauru are expected to add about 2,612 subject years if they maintain their participation in the continued phase. This is independent of the number of births that this group already had (50 births) which by itself lowers the sample size (1582 births) and the subject years required for the continued phase. Therefore, a total of about 18,897 “birth risk” years are targeted in the continued phase to ensure that the minimum estimate of 16,531 subject years is reached. About 5,368 new subjects are thus expected to be enrolled in the study including 1,000 subjects at the Bauru site using the outreach model and 4,368 subjects across the study clinics using the clinic-based model (1,092 subjects per year). Table
10 provides a summary of new subject recruitment and subject years.

**Table 10 T10:** Estimates of new enrollment and subject years

**Site**	**Total of new enrollees**	**Total subject years from new recruitment**
Bauru – Outreach Model	1000	4250
Bauru – HRAC clinic	1248	3439
Salvador	1248	3439
Recife	1248	3439
Porto Alegre	624	1719
*Total*	*5368*	*16281*

Note: The table shows the total number of new subjects estimated to be enrolled by March 2011 and the total subject years estimated to be provided by this recruitment by December 2011.

#### Interim analysis and study monitoring

The DCC will conduct analyses of screening, recruitment, and participation rates as well as analysis of compliance, every quarter of the study. The DCC will compare screening, recruitment, participation, and compliance to the projected rates. If the observed rates are below the expected rates by 20% for any study site, the study team will examine the causes of the discrepancy and develop actions to improve these rates. The DCC will examine the characteristics of dropouts and non-compliers with study procedures and reasons for non-participation when possible. For data quality, error rates will be reviewed from double keying. The DCC will check lab data for consistency of collected information. The birth rates among study subjects will be estimated periodically to determine the number of subjects to be recruited. The DCC will also monitor the generate reports on study adherence and adverse events. A summary monitoring report will be provided to the Data Safety and Monitoring Board (DSMB) for their semiannual meetings.

To examine the efficacy of the intervention, we propose two interim analyses at 40% and 70% of the targeted number of births and a final analysis. The corresponding alpha boundaries are 0.002, 0.017, and 0.031 for a one sided test and unequal spacing of analyses using O’Brien-Fleming spending boundaries
[123]. For the primary hypothesis of this study, the power remains at approximately 80% and the targeted sample size remains sufficient to allow the proposed interim analysis.

All interim analysis reports will be provided to the DSMB for their semiannual meetings. Data will be provided on all the monitored adverse events that are listed in the protocol. The DSMB will review the adverse events by treatment groups, the observed enrollment rate, and the required number of subjects based on observed birth rate at each meeting and make decisions about study continuation. The DSMB will review the rates of primary outcome by treatment groups at each interim look and make decisions about study continuation. The magnitude of any observed rates of primary outcome differences by treatment status and what to consider a "substantial" difference will be revisited at each interim looks.

In addition, conditional power/stochastic curtailment method
[124] may be used if requested by the DSMB due to small observed differences in primary outcome rates between treatments. This analysis involves calculating the conditional probability of rejecting the null hypothesis given a specific alternative and the sample size at the time of the analysis. A very small probability suggests that the null effect may be inevitable.

Sample size and spending boundary estimations were performed using the East version: 4.0.1.50 by Cytel Software Corporation.

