#### Power analysis

Table
8 presents estimates of prospective number of births in the two study groups required for 70 and 80% statistical power and 30, 50, and 70% reductions in CL/P recurrence for alternative recurrence rates of 3, 5, and 7% in the 0.4 mg group. The 30% reduction represents a lower effect that is still very clinically significant, while the 70% represents an effect similar to that observed for NTD recurrence
[118]. The recurrence rates cover most of those reported in the literature and we use the 5% rate as a primary reference for our total suggested sample size given that it represents a proportional estimate of the 4 and 7% recurrence rates assuming that 30% of the study subjects will be women with clefts and 70% will be mothers to children with clefts. The power calculations are based on a Type I error probability of 5%. We use a one sided test as the recurrence rate in the 4 mg is not expected to exceed that of the 0.4 mg group given the converging evidence of protective effects of folic acid; a Fisher’s exact test is used.

**Table 8 T8:** Power analysis for primary hypothesis

**Baseline recurrence rate**	**% Reduction**	**Power**	**Total births**	**Total subject years**
*0.07*	70	0.8	524	5475
		0.7	418	4368
	50	0.8	1114	11641
		0.7	874	9133
	30	0.8	3324	34734
		0.7	2574	26897
*0.05*	70	0.8	742	7753
		0.7	590	6165
	50	0.8	1582	16531
		0.7	1240	12957
	30	0.8	4734	49467
		0.7	3666	38307
*0.03*	70	0.8	1254	13103
		0.7	996	10408
	50	0.8	2676	27962
		0.7	2096	21902
	30	0.8	8024	83845
		0.7	6210	64890

For a 50% reduction in a baseline rate of 5% recurrence, a total of 1582 births distributed equally across the two treatment groups are required. This number of births also provides acceptable power (0.75) to detect a 60% decrease in a 3% baseline recurrence rate, or a 40% decrease in a 7% baseline risk. If the 4 mg dose shows a preventive effect similar to that seen for NTDs (70%), the required numbers of births are halved regardless of the baseline recurrence risk (range from 524 to 1254 births for 80% power). The numbers of births required to observe a 30% reduction are about three times as large those for a 50% reduction.

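### The three printed alpha boundaries (0.002, 0.017, 0.031) are the alpha spent at each look, not p-value thresholds; used as cut-offs they would cost about 5 points of power at 1,582 births

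*Protocol article*

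**What the plan says.** The Power analysis section of the protocol article sets the frame. On the error rate: "The power calculations are based on a Type I error probability of 5" per cent. On direction: "We use a one sided test as the recurrence rate in the 4 mg is not expected to exceed that of the 0.4 mg group". Fisher's test is named ("exact test is used"). The reference case is stated as: "For a 50% reduction in a baseline rate of 5% recurrence, a total of 1582 births", "distributed equally across the two treatment groups", which is 791 per arm.

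Interim analysis and study monitoring adds two interim efficacy analyses, at 40% and 70% of the targeted births, and a final analysis, using O'Brien-Fleming spending. It then states: "The corresponding alpha boundaries are 0.002, 0.017, and 0.031 for a one sided test and unequal spacing of analyses". It also says of the primary hypothesis that "the power remains at approximately 80% and the targeted sample size remains sufficient to allow the proposed interim analysis". The section closes by saying that sample size and spending boundaries were computed in East. The article gives no other p-value threshold and does not say that the three figures are amounts of alpha spent.

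**The concern.** The three figures add up to exactly 0.050. True group-sequential thresholds do not do this. Test statistics at successive looks are positively correlated, so thresholds that spend 0.05 in total must sum to more than 0.05. An exact sum suggests that the spent-alpha column was reported under the name of boundaries.

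A data monitoring board or analyst who took the text literally would compare the final Fisher p-value with 0.031, although the trial's own spending plan allows about 0.044. Results between those values would be reported as negative, and the power would not be the power stated in the same paragraph.

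**Working it through.** **Inputs.** All are from the protocol article: overall one-sided alpha 0.05, Fisher's exact test, 5% versus 2.5% recurrence, and 1,582 births split 1:1 (Power analysis); looks at fractions 0.40, 0.70 and 1.00, O'Brien-Fleming spending, and the printed triplet (Interim analysis and study monitoring).

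**1. Sample size.** The one-sided two-proportion formula with continuity correction, at alpha 0.05 and power 0.80, gives 1,584 births against the stated 1,582. Exact Fisher power at 1,582 births with a single look at 0.05 is 0.810. The sample size is sound.

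**2. Printed triplet.** The O'Brien-Fleming-type spending function is α(t) = 2 − 2Φ(1.960/√t).

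| Fraction t | 1.960/√t | Cumulative α(t) | Increment | Printed |
|---|---|---|---|---|
| 0.40 | 3.099 | 0.00194 | 0.0019 | 0.002 |
| 0.70 | 2.343 | 0.01915 | 0.0172 | 0.017 |
| 1.00 | 1.960 | 0.05000 | 0.0309 | 0.031 |

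The increments round to the printed figures. Two alternatives do not: spending one-sided 0.025 gives increments 0.0004, 0.0070 and 0.0176, and the classical O'Brien-Fleming shape gives nominal p-values 0.0033, 0.0200 and 0.0429.

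**3. Nominal thresholds.** These are solved look by look from a multivariate normal with correlation √(tᵢ/tⱼ), so that the cumulative crossing probability under the null equals α(t):

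- z = 2.887, 2.085, 1.704
- one-sided p = 0.0019, 0.0185, 0.0442

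**4. Printed figures used as cut-offs.** They correspond to z = 2.878, 2.120, 1.866. Normal theory uses drift 1.645 + 0.842 = 2.486, the value for a fixed design with exactly 80% power. The Fisher figures are simulated with 316, 554 and 791 births per arm.

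| | Printed figures as cut-offs | Nominal thresholds |
|---|---|---|
| Overall one-sided alpha, normal theory | 0.038 | 0.050 |
| Overall one-sided alpha, Fisher | 0.029 | 0.038 |
| Power, normal theory | 0.747 | 0.792 |
| Power, Fisher | 0.753 | 0.800 |

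Fisher's test is itself conservative here: a single look at 0.05 has actual size 0.039. So only part of the gap between 0.029 and 0.05 comes from the thresholds.

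**5. Effect of a larger birth yield.** The Sample size section targets 18,897 subject-years at 0.0957 births per subject-year: 18,897 × 0.0957 = 1,808 births. At that number, with the printed figures as cut-offs, simulated Fisher power is about 0.81. By normal theory from an 80% design, about 1,817 births (1,582 × 1.149) would restore 80%.

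**The case against.** The strongest reply is that the article never says the final criterion is p < 0.031. It speaks of alpha and spending boundaries and cites East, and its 80% power reproduces with the nominal thresholds. On that view the software run was correct and the three figures are only loosely named. This is plausible and it limits the point: the fault lies in the reported boundary values, not in the sample size. It does not remove it, because boundaries for a one-sided test are naturally read as cut-offs and no others are given.

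Second, 1,582 births is a floor, and at about 1,808 births the shortfall disappears. This stands as a possibility. It depends on retention and on the assumed birth rate. Subsequent births to the same woman are left out of the first primary analysis, and the looks are most naturally tied to 1,582.

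Third, the error is conservative. This stands in full: the increments used as cut-offs are a valid Bonferroni split, and the three numbers create no excess false-positive risk. An uncorrected z-test would also keep power near 0.80 (0.796 simulated), but the plan specifies Fisher's test.

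A reader might also infer that type I error control is lost, because what counts as a substantial "difference will be revisited at each interim looks". The document does not support this. The sentence concerns the size of rate differences and decisions on study continuation. It does not say that the alpha boundary will be changed or replaced. The board's working is set out in a separate charter that is not shown.

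**Conclusion.** The printed figures are wrong for the role the article gives them. They are alpha spent per look; the matching one-sided thresholds are about 0.0019, 0.0185 and 0.0442. The printed boundaries and the printed power do not fit together at 1,582 births under Fisher's test: about 75% with the figures as cut-offs, about 80% with the nominal thresholds.

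The consequence is conditional. It arises only if the figures are applied as p-value cut-offs and the births analysed are close to 1,582. A reader might conclude that the trial will in fact be tested at 0.031 and is underpowered; the article does not establish either. The calculations assume looks at exactly 40%, 70% and 100% of births, 1:1 allocation, and recurrence of 5% versus 2.5%.

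**What to change.** In Interim analysis and study monitoring, state nominal one-sided p-value thresholds of 0.0019, 0.0185 and 0.0442 for looks at 40%, 70% and 100% of the targeted births. Add that they will be recomputed from the spending function at the birth fractions actually observed. Keep 0.002, 0.017 and 0.031 only if relabelled as alpha spent at each look. Check that the analysis plan and the monitoring board's charter carry the same thresholds.

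The cost is wording only, with no extra births. Keeping the printed figures as cut-offs and buying back the power would take about 1,817 − 1,582 = 235 more births by normal theory, or about 235 / 0.0957 ≈ 2,456 subject-years at the plan's birth rate.

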### Quality control

The quality control plan will involve establishing a competitive set of selection criteria of study personnel, adequate training and certification of training, adequate on-site monitoring of study progress, periodic and on as-needed basis conduction of site visits by principal investigator, NICHD Staff Science Collaborator, and the Data Center, and appropriate provision of guidance and feedback to study personnel upon occurrence of protocol violations. The quality control process also includes the following: verification of data entry, establishing a toll-free phone line for subjects to call for questions, monitoring quality of folic acid pills, providing adequate and continuous guidance to subjects regarding proper intake and handling of pills, and continuous and adequate reporting of adverse events and protocol violations.

#### Selection of study personnel

Selection criteria to be utilized in the recruitment and hiring of study personnel include (1) appropriate educational level, (2) high technical competence, (3) good communication skills, (4) a commitment to and interest in the study design, and (5) quality related professional experience.

#### Job descriptions

Please see Section for job descriptions. The table below lists selection criteria for each position.

#### Training procedures

All study personnel will receive training as outlined in Table
11.

**Table 11 T11:** Staff selection criteria

**Job title**	**Selection criteria**
***Brazil Research Unit Staff***	
Clinical Coordinator (or Study Nurse)	Higher or intermediate schooling level*, high communication skills that allow for conducting successful interviews with subjects, quality skills in drawing blood samples (if needed), as well as acceptable computer knowledge/familiarity that enable them to manage laboratory and patient compliance data.
Data entry person (outreach model only)	Intermediate schooling level*, good skills in using basic computer packages such as Word and/or Excel, as well an acceptable speed of data entry
Drivers (outreach model only)	Fundamental schooling level*, having a driver’s license and showing a mature attitude and responsibility towards driving.
Administrative Assistant	Higher schooling level*, high communication skills that allow coordination of correspondence and meetings with the Principal Investigator and other related personnel, as well as having a very good knowledge of written and spoken English to be able to translate both written and spoken English to Portuguese and vice versa.
***US Staff***	
Study Coordinator	PhD or equivalent degree in a health care related field, good experience in project management and research conduct, as well as strong communication skills and commitment to responsible care.

*The Brazilian Educational System is divided into three levels: fundamental, intermediate and higher education. Fundamental school extends over eight grades. Intermediate school extends over at least three grades, and may include professional training. It thus may last for four or five years and provides professional qualification. Higher education is composed of two different levels: undergraduate (e.g., full-nurse) and graduate. Additionally, professional training may be provided to students who have only completed fundamental school.

#### Certification procedures

All the study personnel will undergo training before data collection commences. The competence of the trainees will be certified at the end of the course and via a post-training test. The Co-Principal Investigators will be responsible for certification.

#### On-site monitoring

At each site, the research will meet on a periodic basis as determined locally to review ongoing activities and assurance of quality control.

#### Site visits

Site visits will be conducted by the Principal Investigator, NIDCR, and the Data Coordinating Center to monitor the quality of study implementation by the Research Units. Site visits will be conducted at least once a year and on an as needed basis (if there are study implementation concerns that seem to require immediate evaluation and/or intervention), in consultation with the local IRBs and will include the participation of the Principal Investigator, NIDCR Program Official and/or Project Officer, and the Data.

Coordinating Center Principal Investigator or his/her designee. The NIDCR, the Data Coordinating Center, and the U.S. and foreign Research Units will collaborate in the planning and implementation of each site visit.

The purpose of a site visit is to monitor study procedures including those related to the protection of human subjects, recruitment and eligibility, data collection and management, the protocol violations, and adverse event reporting.

Methods for monitoring include chart reviews, interviews with research staff, and facility observation. The site visit will include a feedback session to review results and suggest recommendations for improvement. The Data Coordinating Center will submit a report to NIDCR that documents the assessment, results, and feedback given to the Research Units, as well as its recommendations.

#### Feedback for protocol violations

The Co-Principal Investigators will provide guidance and feedback to the appropriate study personnel on any protocol violations. A list of these is provided in Section 4.6. In some cases, retraining or retesting may be indicated. Protocol violations will also be reviewed at weekly staff meetings.

#### Quality control of study pills and randomization

The folic acid pills for the ongoing study are manufactured by ATIVUS Pharmaceutical Industries in Brazil (
http://www.ativus.com.br/). The manufacturer will conduct quality control tests for each batch of pills including identification test of the raw folic acid material used in the pills (prior to production), assay tests for the folic acid dosage in the pills, content uniformity tests (to ensure that the dosage is consistent across pills), and dissolution tests to ensure that the pills dissolve adequately in a standard time. The manufacturer will provide these results to the investigators before labeling and shipping the pills to the sites. If the results are not within the acceptable range, the manufacturer will reproduce and retest new batches of pills. Only batches with documented test results that are within acceptable ranges will be shipped to the sites.

The manufacturer will label the blister packs with lot numbers, enclose the blister packs in boxes, and place the 0.4 and 4 mg boxes in separate containers. An independent contractor will label the pillboxes, at the manufacturer’s facility, with the serial numbers that are matched to randomization assignment. The labeling will be conducted under RTI’s supervision (see section 4.1.1). The accuracy of the labeling will be independently tested, before sending the pills to the sites, through randomly selecting and sending to RTI a sample of boxes that are labeled with the serial numbers. RTI will compare the lot numbers on the blister packs to the serial numbers on the pillboxes to ensure that serial numbers and lot numbers match correctly. Further, the pills from this sample will be sent to an independent laboratory in the US to conduct assay content tests to ensure that the folic acid dose matches the treatment assignment of the lot numbers (0.4 versus 4 mg). These steps will identify errors in labeling the blister packs and in labeling with serial numbers. The latter can result due to incorrect packaging the pillboxes into the 0.4 and 4mg containers by the manufacturer or due to inaccurate serial number labeling by the contractor.

Different procedures will be used to address labeling errors depending on the error type. Errors in serial number labeling will require verifying the lot numbers inside each pillbox to ensure that they match the assigned serial number and relabeling those that do not match. All the pillboxes will be rechecked when this error occurs. Errors in blister pack labeling will require production and labeling of new pills, which will be test using the procedures described above.

Pills will not be sent to the sites before all the quality control procedures are completed. This necessitates that pill orders are placed at least 5 months before the intended date of shipping to the sites.

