#### Randomization procedures

Study subjects will be randomized to either 4mg or 0.4mg of folic acid. The study will be double-blinded; subjects, investigators and research staff will be blinded to the randomization assignments.

The Data Center will prepare the randomization sequence for the study using permuted blocks of random size. Randomization occurs at the subject level and is stratified by study site to ensure a balanced site representation in both treatment groups. The randomization will not be stratified according to risk group (mother with oral cleft or mother of child with oral cleft) or other factors due to the large sample size. As shown in
[121], stratification becomes irrelevant after the sample rises above 200 subjects. Since randomization occurs at the mother’s level, the sample allocation should be very well balanced with respect to the risk group and other factors.

The randomization sequence will link the treatment assignment (0.4mg or 4mg) to a sequential list of serial numbers to be used for the study pill boxes. The Data Center will generate the randomization sequence. The Data Center will supervise the labeling of the boxes with the serial number. In addition, the boxes will be numbered in order of dispensing (1, 2, 3, etc.3). The serial and dispensing order numbers will be recorded on the study visit/follow-up form to track dispensing.

The random assignment will be accomplished by assigning the next serial number in the randomization list as the enrollment of each new subject is confirmed. Once confirmed, the study subject ID is recorded in a computerized randomization log (that will include randomization order, serial number of assigned pill box and the study subject ID). The Clinical Coordinators will affix the study subject ID labels to the boxes of each subject with the serial number assigned to her.

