#### Study treatments

The study drugs are folic acid in concentrations of 4mg (high dose) and 0.4mg (low dose). The study drugs are supplied in tablet form, manufactured by ATIVUS Pharmaceutical Industries in Sao Paulo, Brazil. Quality control assessments of samples of production batches will be performed for all manufacturers in an independent quality control lab in the United States (Celsis Laboratory Group, Saint Louis, US). All pills, regardless of their folic acid concentration, will be identical in size, shape, and color and will be provided in identical packaging. Patients enrolled in the study will be instructed to ingest 1 tablet daily from enrollment until 3 months gestation.

The manufacturers will package the folic acid pills in boxes containing 5 blister packs of 14 pills each (2 rows of 7 pills), for a total of 70 pills per box. Each box will contain an information sheet that will include all recommendations of the country’s drug monitoring agencies (ANVISA for Brazil) regarding information about the drug, yet will not reveal in any way the actual folic acid content. The manufacturer will also label each of the pill boxes with the following information, in addition to any other item that is recommended by the monitoring agency:

Manufacturing and expiration dates (including only the month and the year of production which will be common for the two doses of folic acid)

Description of the drug (folic acid)

Identification of the manufacturer

Statement about the use of the drug (“this product is solely intended for research use and shall not be commercialized”)

Patient instructions for taking pills (or if a daily dose is missed)

Clearance number of monitoring agency

Clinic’s logo

The manufacturers will also label the blister packs with a production lot number. Each production run of pills will use several lot numbers for each dose. The lot numbers pertaining to each dose will be sent from the manufacturer directly to RTI after each production run.

After each production, RTI staff will supervise labeling the pillboxes with a serial number (##### - ##, a seven digit number with 5 digit base number and 2 check digits). A local staff independent of the study may be used to label the pill boxes.

There will not be any information on the pill box or blister pack that may indicate to the subject the folic acid content of the pills.

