#### Delivery of interventions (Treatments)

An 8-week supply of study pills will be dispensed to subjects upon enrollment and at regular 8 week intervals to ensure uninterrupted dosing during the preconception and prenatal periods of participation. Study pills may be dispensed during in-person visits or delivered to subjects through express mail or in person visits to the clinic or subject’s home. In all sites, the pillbox provided for the previous supplementation period will be obtained from the subject to determine pill compliance.

Subjects who are confirmed to be pregnant will be advised as when to stop taking the study pills so that the intervention is limited to the first three months of gestation. If a subject experiences an adverse event, the study medication may be discontinued either temporarily or permanently after review of the principal or co-principal investigator and depending on the recommendation of the physician attending the subject when applicable.

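### Batch dosage-assay results go to the blinded investigators although blister packs carry dose-specific lot numbers, leaving an avoidable route to unblinding

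*Protocol article*

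**What the plan says.** All references are to the protocol article.

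- **Who is blinded.** Randomization procedures: "subjects, investigators and research staff will be blinded to the randomization assignments".
- **What is printed on the packs.** Study treatments: "The manufacturers will also label the blister packs with a production lot number", and "Each production run of pills will use several lot numbers for each dose".
- **Who holds the key.** Same section: "The lot numbers pertaining to each dose will be sent from the manufacturer directly to RTI after each production run".
- **The stated assurance.** Same section: "There will not be any information on the pill box or blister pack that may indicate to the subject the folic acid content". It is worded for the subject and does not mention staff.
- **Who receives the batch tests.** Quality control of study pills and randomization lists identification, dosage assay, content uniformity and dissolution tests for each batch, and then says "The manufacturer will provide these results to the investigators before labeling and shipping the pills to the sites". No unblinded recipient is named, and nothing is said about removing identifiers.
- **Who handles used packs.** Delivery of interventions (Treatments): at all sites "the pillbox provided for the previous supplementation period will be obtained from the subject to determine pill compliance".

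**The concern.** The protocol treats the link between lot and dose as sensitive: it sends the list straight to RTI and keeps it from the sites. In a later section it sends results that include the measured dosage of each batch to people it has declared blinded. The two arms differ tenfold in content (4 mg against 0.4 mg), so a dosage assay for a batch states which arm that batch belongs to. Whether this opens the blind depends on whether the reader of the report can connect the batch to packs that women hold.

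The stake is the double-blind design, which the article presents as its main advance on earlier interventional and observational work. Under Follow-up of study subjects, the Clinical Coordinator or Co-Principal Investigator examines infants, and gestational losses are reviewed by the coordinator, the Co-Principal Investigator or clinic geneticists. Co-Principal Investigators also decide on requests to reveal an assignment and share in decisions to stop study pills after adverse events. Knowledge of dose could influence who is kept in follow-up, how losses are classified, how hard other birth defects are looked for, and how cleft severity is scored. The presence of a cleft is verified by clinical examination and is less open to this, although differential retention could still affect which births are counted.

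**Working it through.** There is no figure in the plan to reproduce. The check is to set the provisions side by side.

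1. **Is the lot number a dose code?** Yes, by the protocol's own use of it. Study treatments gives several lot numbers to each dose. Under Quality control of study pills and randomization, RTI compares blister lot numbers with box serial numbers, and the independent US assay then checks that the dose agrees with the arm to which the lot numbers belong. That procedure works only if each lot holds one dose.
2. **Does site staff see the lot number?** They can. It is on the blister packs inside the box, and the used box is recovered to assess compliance. Computer hardware and software provides for counts of unused pills to be kept on the study clinics' computers.
3. **Who is meant to hold the lot-to-dose link?** RTI only, under Study treatments.
4. **Who receives dosage results by batch?** The investigators, before labelling and shipping.
5. **Are those recipients blinded?** Yes, under Randomization procedures. Some of them, the Co-Principal Investigators, also assess outcomes.

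Steps 3, 4 and 5 do not fit together as written. Two routes to unblinding follow.

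- **Route A, through the assay report.** It needs the report to be identifiable by batch or lot and that identifier to be traceable to the printed lot number. The text does not state this. It is plausible, because only batches with documented acceptable results may be shipped, so results must be traceable to batches at some level.
- **Route B, through one disclosed assignment.** It does not depend on the assay report. Randomization procedures permits an assignment to be revealed for clinical need, and Protocol violations anticipates inadvertent disclosure. Since each lot holds one dose, learning one woman's dose and seeing her lot number gives the dose of every other woman on that lot.

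**Size.** If a run uses L lots per dose, equally and randomly filled, one known lot covers about 1/L of an arm for that run. The documents do not give L. Purely as an illustration, an assumed L of 3 gives 1/3 = 33% and an assumed L of 10 gives 1/10 = 10%. Neither is an estimate for this trial.

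**The case against.** The strongest reply is that the damaging step is not in the text. No provision says that the results carry printed lot numbers or that a tested batch is the same thing as a lot. With several lots per dose in each run, a batch may span several lots. The results also arrive before labelling. An investigator told that one 4 mg batch and one 0.4 mg batch have passed learns nobody's assignment. Most contact with women falls to the Clinical Coordinators, to whom no provision sends assay results. Code breaks are tightly restricted, and the lot list goes only to RTI. All of this stands, and it limits the point to a possible route.

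Three stronger readings are tempting and are not supported:

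- **That the lot number contradicts the assurance about pack information.** That assurance concerns the subject, and a lot number without its key tells her nothing. The conflict is with the blinding of investigators and staff.
- **That allocation concealment is broken.** Lot numbers sit inside the box, and assignment takes the next serial number once enrolment is confirmed. Reading a future assignment would need the key and an opened, undispensed box. The article does not say whether boxes are sealed.
- **That nearly every woman's dose could be read.** With 3 to 10 assumed lots per dose, random filling and successive runs linking lots through shared women, one can calculate near-complete identification of an arm. That also requires someone to record and pool lot numbers deliberately. The follow-up forms are to record serial and dispensing-order numbers, and site databases are kept separate. It is not an expected effect.

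What the reply does not answer is why blinded investigators should receive dosage results at all, when RTI already holds the key.

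**Conclusion.** The point holds as an unreconciled provision and an avoidable route to unblinding. It does not show that the blind is or will be broken. The text establishes that lot numbers are dose-specific and printed on dispensed packs, that the key is meant for RTI alone, and that batch results including the dosage assay go to investigators declared blinded. It does not establish that those results can be matched to the printed lots.

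The exposure is to blinding in retention, miscarriage review, other birth defects and severity scoring, and much less to concealment or to the presence of a cleft at examination. Its size cannot be derived from the documents, since it depends on the number of lots per dose, how boxes are filled and distributed, and how the reports are identified. The case for acting is that the remedy costs almost nothing and removes the route that the protocol itself writes down.

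**What to change.** In Quality control of study pills and randomization, change the recipient: the manufacturer's assay, content uniformity and dissolution results go to RTI only. RTI reviews them and sends the investigators a pass/fail release statement with no dose, batch or lot identifier. This brings the section into line with Study treatments and Randomization procedures.

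Do not replace the lot numbers with one code common to both doses. RTI compares blister lots with box serial numbers to catch boxes placed in the wrong dose container, and after a serial-labelling error every box is rechecked by the lot inside it. A common code would disable both checks.

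As an option, print a scrambled code on the packs with the key held by RTI, if the manufacturer can do so and the drug agency accepts it. That would narrow the route through a single disclosed assignment, which re-routing the reports does not touch.

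Cost: a change of protocol and manual wording and of addressee, with RTI taking on review and release of each batch. No extra participants, visits or staff, and the pill quality checks stay as they are.
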